### Secondary end points

The following are the secondary end points:

1. The time from the first dose of study medication to the start of first 24-hour diarrhoea-free period as recorded by parents or guardians in an hourly checklist, which will be collected by the nurses on duty every 12 hours.

2. Treatment failure, defined as the occurrence of (a) No resolution of diarrhoea after 5 days of treatment, (b) severe symptoms for which treatment is stopped, such as the development of severe dehydration, renal failure, (septic) shock, respiratory distress or other syndromes associated with diarrhoeal disease as complications (e.g., pneumonia) [5]; and (c) additional antiemetic (domperidone) or antidiarrhoeal (aluminium silicate or racecadotril) treatment.

3. The frequency of stools during the first 3 days after the first dose of study medication.

4. The load in copies per millilitre of viral transport medium of norovirus and rotavirus measured by RT-PCR, assessed daily from admission until discharge and at follow-up.

5. The duration of hospitalisation, defined as the number of days from hospital admission until discharge.

6. The extent of intestinal *L. acidophilus* colonisation, assessed by analyses of faecal samples or rectal swabs collected on admission, on discharge and at outpatient follow-up for the first 50 participants who agree to participate.

7. The number and severity of AEs.

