### Sample size and statistical considerations

Data originating from three hospitals in Ho Chi Minh City suggest that the median duration of hospitalisation in our target population is 5 days (interquartile range = 3 to 6 days; mean and standard deviation [SD] of log_10_ duration = 0.61 and 0.27, respectively) and an approximately normal distribution of the log-transformed data. As we have limited preexisting data on the overall length of diarrhoeal illness (prehospitalised and hospitalised), and as children are usually discharged at the time of resolution of diarrhoea, we used the variability of the length of hospitalisation as the basis of our sample size calculation using R software version 2.15.1. This study is designed to test the hypothesis that probiotic therapy is superior to placebo for the treatment of acute watery diarrhoea. It is powered to detect a 20% decrease in the duration of acute watery diarrhoea (corresponding to an absolute effect size of approximately 24 hours) of twice the standard dose of probiotics compared to placebo. For 80% power with a two-sided 5% significance level, a total of 123 participants per study group are required. To account for potential inadequacies in our assumptions and some loss to follow-up, the sample size was increased by 22%. Therefore, a total sample size of 300 participants (150 in each group) will be recruited.

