### Analysis and reporting

All randomised patients will be included in the analysis, following the intention-to-treat principle. The comparison of the primary end point will be performed on a per-protocol population, which excludes participants who are mistakenly randomised (in violation of the inclusion and exclusion criteria) and those who withdraw or are lost to follow-up prior to reaching the primary end point.

The primary end point will be compared between the study arms on the basis of a lognormal accelerated failure time regression model, which models the log-transformed outcome as depending linearly on covariates plus a normally distributed error term for unexplained variation [27]. It generalises the standard linear regression model of the log-transformed outcome to right-censored or interval-censored outcome data that are required for analysing our primary end point. If parents or guardians cannot specify the exact time of cessation of diarrhoea, then the assessment by the nurse on duty who assesses the child every 12 hours will be used instead (treated as an interval-censored outcome).

Children who are withdrawn or lost to follow-up before the cessation of diarrhoea will be treated as censored on the day of withdrawal or loss. The primary analysis will not adjust for any covariates, but, in a second step, we will additionally explore the effect of the following covariates on the duration of diarrhoea: duration of diarrhoea prior to enrolment, prior treatment with antibiotics and prior treatment with probiotics, age and diagnosed pathogen by culture or PCR. Likewise, homogeneity of the treatment effect will be assessed according to the subgroups defined by these. The secondary end point of the time from the first dose of study medication to the start of the first 24-hour diarrhoea-free period as assessed by the parents or guardians will be analysed in the same way as the primary end point. Other secondary end points will be compared between the treatment arms on the basis of logistic regression for binary data, Poisson regression for count data, linear regression for continuous data and the lognormal accelerated failure time model for time-to-event data. The comparison of viral load outcomes for norovirus and rotavirus detected by RT-PCR will be adjusted for the participant’s baseline viral load to increase power.

The results of this trial will be reported in one or several peer-reviewed publications.

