The nurse on duty will measure the reduction of diarrhoea duration after the start of treatment and the effect of probiotics on the total duration of diarrhoea in 12-hour intervals. As nursing staff assess patients at least every 12 hours, it is efficient to include the study assessments and data collection at those points in time. Children who participated in our previous cross-sectional study in three hospitals in Ho Chi Minh City were discharged after a median of 5 days (range, 1 to 22 days). It is difficult to collect reliable data on daily stool frequency after discharge; therefore, we have chosen to analyse stool frequency only during the first 3 days of hospitalisation. It is imperative to have a laboratory measurement for the effect of probiotics on diarrhoea; therefore, we have additionally selected the viral loads of norovirus and rotavirus in faeces as a secondary end point, as these organisms are the most common cause of acute watery diarrhoea. Norovirus and rotavirus viraemia have been described previously, and rotavirus antigenaemia has been associated with rotavirus viraemia [31,32]. We have also included an exploratory analysis on the load of norovirus and rotavirus in the blood of participants with the aim of investigating viral presence and viral load in those who test positive for norovirus or rotavirus in the stool. The ability of probiotics to colonise the intestinal tract is one of the definitions of a probiotic [33]. Colonisation by probiotics is reported to occur after several days of treatment and is reported to be transient and last for an ill-defined time period [34-37]. Hence, we have included a further secondary end point investigating the colonisation of *L. acidophilus* in faecal samples by culture and molecular techniques before treatment, at discharge and at follow-up.

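### Poisson regression is named for count end points with no allowance for overdispersion, so the test on 3-day stool frequency very probably exceeds its nominal 5% size

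*Protocol article*

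**What the plan says.** Under Analysis and reporting, the protocol article assigns the remaining secondary end points to models by data type. For counts the entry is "Poisson regression for count data". No dispersion parameter, robust variance or alternative count model is mentioned.

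The third item under Secondary end points is "The frequency of stools during the first 3 days after the first dose of study medication". The analysis section does not link this item to the Poisson model by name, but it is the obvious count among the listed end points.

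The Discussion describes the window differently: "we have chosen to analyse stool frequency only during the first 3 days of hospitalisation".

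**The concern.** A Poisson model sets the variance equal to the mean. That fits if every child has the same expected 3-day total. The article's own description suggests otherwise:

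- Length of stay, which the sample size section uses as a stand-in for duration of diarrhoea, is widely spread on the log scale.
- The Discussion reports that rotavirus, norovirus or both account for a little over 60% of cases, so causes are mixed.
- Ages run from 9 to 60 months, and illness before entry may last up to 3 days.

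If counts are Poisson given each child's own rate and duration, mixing over such children pushes the variance above the mean. Standard errors taken from the Poisson model would then be too small, and a chance difference between arms would be called significant more often than 5% of the time. Stool frequency is one of the secondary end points named in the abstract, and a positive result would be read as support for the primary.

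**Working it through.** **1. The plan's own figure.** The article gives no calculation for stool frequency. Its only calculation concerns the primary end point: "It is powered to detect a 20% decrease in the duration of acute watery diarrhoea", with mean and "standard deviation [SD] of log_10_ duration = 0.61 and 0.27, respectively".

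- Effect on the log10 scale: |log10 0.8| = 0.0969.
- Normal approximation: 2 × (1.960 + 0.842)² × (0.27 / 0.0969)² = 2 × 7.849 × 7.764 = 121.9, so 122 per group. The two-sample t-test version gives 122.8, so 123.
- Increase: 123 × 1.22 = 150.06, so 150 per group.

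The stated 123 and 150 reproduce. They do not bear on the stool-count analysis.

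**2. Effect of overdispersion on the test.** Let φ = variance / mean. The model-based Poisson standard error is too small by a factor √φ, so the true size of a nominal 5% two-sided test is 2 × [1 − Φ(1.96 / √φ)].

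| φ (assumed) | 1.96 / √φ | True size |
|---|---|---|
| 1 | 1.96 | 5% |
| 2 | 1.39 | 17% |
| 3 | 1.13 | 26% |
| 4 | 0.98 | 33% |
| 5 | 0.88 | 38% |

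**3. What the documents can say about φ.** For a Poisson mixture φ = 1 + mean × CV², where CV is the coefficient of variation of the children's expected totals. Only the duration part can be drawn from the article, taking hospital stay as proxy, a constant stool rate until cessation and no stools afterwards.

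- Share stopping within 3 days: Φ[(log10 3 − 0.61) / 0.27] = Φ(−0.49) = 31%.
- CV of ill time within the 3 days (simulated): 0.19, so CV² = 0.037.

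Between-child variation in stool rate (CVr) has to be assumed. The two parts combine as CV² = (1 + 0.037) × (1 + CVr²) − 1. For an assumed mean of 15 stools:

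- CVr 0: φ = 1 + 15 × 0.037 = 1.56, true size 12%.
- CVr 0.3: CV² = 0.130, φ = 2.96, true size 25%.
- CVr 0.5: CV² = 0.296, φ = 5.45, true size 40%.

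**4. Wider assumptions.**

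- *Upper end.* Take 4 to 8 stools a day while ill, CVr from 0 to 0.5, no stools after cessation, and stay with or without its last 24 hours removed. (The protocol discharges children 24 hours after symptoms cease, while the sample size section says discharge usually coincided with resolution.) Then φ runs from 1.4 to 9.1 and the true size from 10% to 52%.
- *Lower end.* Take 4 stools a day while ill, 2 a day after cessation, CVr 0 and full stay. Then φ = 1.10 and the true size is 6%. With the last 24 hours removed, φ = 1.30 and the true size is 9%.

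**5. Does the remedy work?** Gamma-Poisson counts were simulated with 150 per arm, a mean of 15, no treatment effect and 10,000 replicates.

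| CV between children | Poisson standard error | Sandwich standard error |
|---|---|---|
| 0.3 | 19.8% | 4.9% |
| 0.4 | 28.8% | 4.8% |
| 0.5 | 37.2% | 5.1% |

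**6. The window.** The end point list starts the clock at the first dose; the Discussion starts it at hospitalisation. The two need not coincide: children are approached after routine admission, and undecided parents have until 72 hours after disease onset to consent.

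**The case against.** The strongest reply is that one clause in a condensed article names model families, not variance estimators. Poisson regression with a sandwich variance is still Poisson regression, so the text does not forbid the remedy, and an analysis plan that is not shown may already specify it. This stands in part: the clause is compatible with a sound analysis. But the article has chosen a specific model whose default errors very probably fail here, and the same section does go into detail elsewhere, for example on interval censoring and on baseline viral load.

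The second reply is that the extent of overdispersion is unknown. This stands in full. The article gives no mean, SD or dispersion for stool counts. The end point counts stools, not diarrhoeal stools, so a child free of diarrhoea still contributes, which narrows the differences between children. Regular stooling within a child could also offset part of the excess variance.

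A reader might infer three further faults that the document does not support:

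- *Person-time.* Early discharge might seem to bias the rates through an offset for observed time. The article proposes no such offset.
- *Hours after discharge.* It might seem natural to count these as zero stools. They are unobserved and need not be zero, and filling them in that way would favour the arm discharged earlier.
- *Adverse events.* The same criticism might be extended to their number. The analysis section does not assign adverse events to the Poisson model, and the Background calls them rare with probiotics; with low counts φ stays near 1.

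**Conclusion.** The point holds as a weakness in the named model for a secondary end point. Overdispersion of 3-day stool totals is very probable, and Poisson model-based errors would then give a test above its nominal size. At an assumed variance-to-mean ratio of 2 to 4 the true size is about 17% to 33%; across the wider assumptions above it is about 6% to 52%.

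It would be tempting to state as fact that stool counts vary far more than Poisson and that false positives run at several times 5%. The documents do not support that certainty: they give the spread of hospital stay but nothing on stool rates, and the low end of the range is barely above nominal.

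Stool frequency is one of seven secondary end points. The primary lognormal model and the sample size of 300 are untouched. The two window origins are a smaller wording conflict on the same end point.

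**What to change.** In Analysis and reporting, state that total stools in the first 3 days after the first dose will be compared by negative binomial regression, or by Poisson regression with a robust (sandwich) variance. In the Discussion, change the window from the first days of hospitalisation to the first 3 days after the first dose, to match the end point list.

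This takes one clause of analysis text and one of wording, with no new data. Intervals widen by about √φ relative to model-based Poisson: √2 = 1.4 times at φ = 2 and √4 = 2 times at φ = 4. If the counts turn out close to Poisson, almost nothing is lost.

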### Study design

This study is a multicentre, randomised, double-blind, placebo-controlled trial designed to assess the effect of adjunctive probiotic (*L. acidophilus*) therapy in children admitted to the hospital with acute watery diarrhoea. Laboratory endpoints from admission until discharge will be recorded, and colonisation will be assessed in an outpatient follow-up visit with the first 50 subjects who agree to prolonged participation.

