## Discussion

Diarrhoeal disease in young children remains common in low- and middle-income countries such as Vietnam. The main therapy for diarrhoea consists of ORS and zinc, which are frequently supplemented with antimicrobials in severe cases with a suspected bacterial aetiology. Our recent work corroborated findings pertaining to the aetiology of diarrhoea and the accepted clinical practice of treating children hospitalised with acute watery diarrhoea in Ho Chi Minh City. We found that more than 60% of paediatric diarrhoeal cases were due to rotavirus, norovirus or a mixed infection with both ([name] *et al.*, unpublished manuscript).

Probiotic products are frequently used for purposes other than those for which they were originally commercialised, namely, as medication instead of as food. The use of probiotics outside medical settings is also common in Vietnam. Probiotic brands are available inexpensively without prescriptions, and food products and formula milk are frequently supplemented with probiotics. As shown by several studies demonstrating that misidentification is the predominant cause of microbial mislabelling, there is a clear need for better quality assessment of probiotic products, specifically in regard to discrepancies between labels and the actual microbial content [28,29]. Therefore, we considered the use of a probiotic brand that is registered as a drug by the Vietnamese Ministry of Health and is produced according to international standard practices. Furthermore, we intend to ensure the consistency of the study medication by performing quality assessments at multiple time points throughout the trial.

Published studies on the effect of probiotics in treating acute watery diarrhoea in children have compared one or more of the following end points: reduction of diarrhoea duration, stool frequency, hospitalisation duration, virus in faeces and evidence of colonisation of probiotic bacteria. We will record all of these variables in an attempt to perform the most comprehensive study possible. Furthermore, we have taken into account recently published recommendations for future clinical trials using probiotics by the International Scientific Association for Probiotics and Prebiotics [30].

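### Baseline adjustment is stated for viral load only, although *L. acidophilus* colonisation also has an admission value and is compared in only about 25 children per arm

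*Protocol article*

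**What the plan says.** Three parts of the protocol article bear on this.

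- **Analysis and reporting.** Secondary end points other than the parent-recorded time to cessation are compared between arms "on the basis of logistic regression for binary data, Poisson regression for count data, linear regression for continuous data", with a lognormal accelerated failure time model for times to event. No covariate is named there. The next sentence gives the single exception: "The comparison of viral load outcomes for norovirus and rotavirus detected by RT-PCR will be adjusted for the participant’s baseline viral load to increase power". Second-step covariates, which include earlier probiotic treatment, are to be explored for duration of diarrhoea only.
- **Secondary end points, item 6.** The extent of colonisation is "assessed by analyses of faecal samples or rectal swabs collected on admission, on discharge and at outpatient follow-up for the first 50 participants who agree". The Discussion confirms that the first measurement precedes dosing, with an end point "investigating the colonisation of *L. acidophilus* in faecal samples by culture and molecular techniques before treatment, at discharge and at follow-up".
- **Study design.** The same subset is described a little differently: "colonisation will be assessed in an outpatient follow-up visit with the first 50 subjects who agree to prolonged participation". Table 1 lists an admission faecal sample for every child. It is therefore not fully clear whether 50 limits all three time points or mainly the follow-up visit. The comparison after treatment is small on either reading.

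**The concern.** The article adopts a principle (use the pre-treatment value of a laboratory outcome to gain power) and applies it to one repeatedly sampled laboratory outcome but not to the other. Colonisation has the same structure as viral load, and the smaller sample.

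The article also gives reasons to expect that carriage at entry is neither zero nor uniform. In the sponsor's earlier cross-sectional study, 11% of children had received probiotics before hospitalisation. The Discussion adds that "food products and formula milk are frequently supplemented with probiotics". Earlier probiotic use is not an exclusion criterion, and randomisation is stratified by centre only.

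If the admission value is left out, variation in existing carriage stays in the error term. In about 50 children, a chance difference at entry would then feed into the estimated effect on colonisation. What is at stake is how precisely one small secondary end point is estimated. The Discussion includes that end point because the ability to colonise is part of how a probiotic is defined.

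**Working it through.** **The plan's own figure.** The article gives no power, SD, carriage rate or correlation for colonisation. Its only sample-size figure concerns the primary end point, and it reproduces. A 20% decrease is −log10(0.8) = 0.0969 and the SD is 0.27, so n = 2 × [0.27 × (1.960 + 0.842) / 0.0969]² = 121.9 per group. The t-test version gives 122.8, that is, 123. Then 123 × 1.22 = 150.06, or 150 per group. Nothing below alters this.

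**Inputs for colonisation.**
- From the article: 50 children and 1:1 allocation, so about 25 per arm. The split need not be exact, because the subset depends on consent.
- Assumed: a continuous outcome (for example, log quantity); rho from 0 to 0.7; for illustration, a true difference of 0.8 SD; two-sided 5% level.

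**Precision.** Adjusting for baseline multiplies the variance by (1 − rho²). In SD units the standard error is √(1 − rho²) × √(2/25), where √(2/25) = 0.283. The difference detectable with 80% power is 2.802 times that standard error (normal approximation).

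| rho | Variance cut | Detectable difference (SD) | Power at 0.8 SD | Equivalent total n = 50/(1 − rho²) |
|---|---|---|---|---|
| 0 (unadjusted) | 0% | 0.79 | 81% | 50 |
| 0.2 | 4% | 0.78 | 82% | 52 |
| 0.3 | 9% | 0.76 | 84% | 55 |
| 0.5 | 25% | 0.69 | 90% | 67 |
| 0.7 | 49% | 0.57 | 98% | 98 |

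A t-test calculation gives slightly lower power with the same pattern: 79% unadjusted, then 83%, 89% and 97% at rho 0.3, 0.5 and 0.7.

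**Chance imbalance in carriage at entry.** For an assumed carriage proportion p, the SD of the difference between arms is √(2p(1 − p)/25). The probability of a gap of 20 points or more comes from the exact binomial distribution.

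| Assumed p | SD of gap, 25 per arm | P(gap ≥ 20 points) | SD of gap, 150 per arm |
|---|---|---|---|
| 11% | 8.8 points | 4% | 3.6 points |
| 30% | 13.0 points | 16% | 5.3 points |
| 50% | 14.1 points | 20% | 5.8 points |

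The 11% row borrows the figure for earlier use of any probiotic. It is not a measured rate of *L. acidophilus* carriage.

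**What such an imbalance does.** A one-SD chance imbalance at baseline moves an unadjusted continuous comparison by rho × 0.283. That is 0.06 SD at rho 0.2, 0.14 SD at rho 0.5 and 0.20 SD at rho 0.7. Against the illustrative 0.8 SD effect, these shifts are 7%, 18% and 25%.

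**The case against.** The strongest reply is that the article contradicts nothing. It names model families, all of which can take a baseline term. Where it rules covariates out, it says so, and only for the primary analysis. Covariates for the sixth secondary end point are what a condensed article may leave to the full protocol or analysis plan. The admission sample also belongs to the end point's own definition, so it might enter as a change or as new acquisition.

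Much of this stands. A reader might infer that the plan fixes an unadjusted comparison and discards the admission value. The text does not say so, and it leaves open both the form of the outcome and the time point compared. What remains is that the article does address baseline adjustment of secondary end points, gives its reason, and then names only one of two outcomes to which that reason applies.

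Three other strong readings also go beyond the documents:

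- **Bias.** Randomisation keeps the unadjusted comparison unbiased on average, and its standard error already allows for chance imbalance.
- **An imbalance that swamps the effect.** The shifts calculated above are a fraction of the illustrative effect. The larger probabilities of a 20-point gap need carriage of 30% or 50%, which the article does not report.
- **The same remedy for three-day stool frequency.** The article gives a threshold for entry and lists an assessment of diarrhoea at admission. It does not show that a numeric stool count before the first dose is collected, so it cannot be faulted for not using one.

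**Conclusion.** The point holds as a minor one. Baseline adjustment is stated for viral load only. The same rationale covers colonisation, which has a pre-treatment value and the smaller sample, yet no sentence applies it there.

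The possible loss is precision and protection from chance imbalance. For a continuous outcome the variance cut runs from 4% at rho 0.2 to 49% at rho 0.7, so the gain is negligible at the low end and material from about 0.5. It is small if carriage at entry is rare. These figures rest on an assumed correlation, about 25 children per arm and a continuous outcome; they do not carry over to a detected yes/no analysis.

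A reader might also infer that the colonisation result will decide how a null primary result is explained. The article does not say so. The primary analysis and the sample size are untouched.

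**What to change.** Extend the viral-load sentence under Analysis and reporting to cover colonisation, for example:

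> *Comparisons of norovirus and rotavirus load, and of L. acidophilus colonisation, will each include the child's own admission value as a covariate; for colonisation this will be on the log scale if the result is quantitative and as detected yes/no if it is binary.*

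If the full protocol or analysis plan already specifies this, a pointer to it is enough. Leave stool frequency out of the sentence.

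**Cost.** One sentence and one degree of freedom in the model (50 − 2 = 48 residual degrees of freedom become 47 with 50 children). No new samples are needed, because admission specimens are already planned for this end point. The Trial status section says recruitment has not started, so the choice can be fixed before any data exist. That also removes a later choice between adjusted and unadjusted results.
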